### Outcomes

*Primary Outcome Measure*

The success of the intervention is defined as statistically significant more reduction in mean score of PSS-10 in the intervention group as compared with the control group at 12 weeks. The primary outcome measure will be Perceived Stress Scale-10 Items (PSS-10). The PSS-10 is a ten item self-reported scale to assess respondents’ global level of perceived stress (36). Respondents were required to rate the frequency of certain feelings they experienced over the past month on a 5-point Likert Scale (1=never, 2=rarely, 3=sometimes, 4=often, 5=always). It has shown to predict the range of health-related outcomes presumed to be associated with appraised stress (36). The PSS-10 has been translated in Chinese and shown acceptable reliability and validity in both adults (37, 38) and adolescents (39).

*Secondary Outcome Measures*

For secondary outcome meansures, the success of the intervention is defined as statistically significant more reduction in mean score of DASS-21 and statistically significant more increase in mean score of ORS and CISS-SFC in the intervention group as compared with the control group at 12 weeks. Negative mental health outcome will be measured using Depression, Anxiety and Stress Scale (DASS-21). DASS-21 consists of 21 items. Each item is rated on a 4 Likert scale ranging from 0 to 3, indicating to what degree each statement applied to participants over the past week. Summed scores range from 0-42 with more severe symptoms indicated by higher scores. This study will utilize total scores in addition to subscale scores. DASS-21 has been validated in Chinese adolescents and proved to have satisfactory psychometric properties in Chinese adolescent population (40).

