### Sample size

According to a meta-analysis on internet interventions on stress reduction (45), which reported that the overall mean effect size for stress at posttest was Cohen d=0.43 (95% CI 0.31-0.54). Significant, small effects were found for depression (Cohen d=0.34, 95% CI 0.21-0.48) and anxiety (Cohen d=0.32, 95% CI 0.17-0.47). Following this meta-analysis, we therefore choose effect sizes of d=0.43 for perceived stress, d=0.34 for depression and d=0.32 for anxiety. An absolutely reduction of 4.03 points is chosen as minimum clinically significant difference according to a previous study that analyzed PSS-10 scores in terms of minimum clinically significant important difference (MCID) (46). Based on this expected difference, no expected PSS-10 change in the control group, a population mean PSS-10 of 13.7 (SD=5.6) equal between groups (47), a sample size of 172 (n=86 in each study group) is required to detect effect size of d=0.43 with a power (1− β) of 0.80 with alpha of 0.05. A sample size of 192 (n=96 in each study group) will be needed when allowing for 10% drop out. Considering the availability of target sample, we will choose a sample size of 300 (n=150 for each study group).

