### Recruitment

Participants will be recruited from grade 10 and 11 at Mianyang Dongchen International School (MDIS) and Mianyang Nanshan High School (MNHS). MDIS has a student population of more than 2000 in grade 10 and 11. MHS has a student population of more than 3500 in grade 10 and 11. More than 90 percent of high school students (total n= 4950 students) in MDIS and MHS own a mobile phone, and both schools allow students to use mobile phones on the weekends. Recruitment strategies for the trial will involve posters, flyers, advertisement and announcements in class in those two schools. Students who are self-identified as feeling stressed will be recruited. For all participants, consent forms will be read and signed by themselves, their guardians and their head teachers.

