## Methods: Data collection, management and analysis

### Data collection methods

Data relating to perceived stress, negative mental health outcome, positive mental health outcome and coping behaviours will be collected at baseline (T0=0 weeks), post-intervention (T1=12 weeks) and follow-up (T2=16 weeks). Demographic data will only be collected at baseline (see Table1 for study variables). All data will be collected online via the mobile intervention app.

Baseline variables, including demographics, will be gather at the start of the study (Table 1).

Table 2 Study variables

| **Variable** | **Measure** |
| --- | --- |
| Demographic | Age |
|  | Gender |
|  | Grade |
|  | Home location (rural or urban) |
|  | Guardian (parents or others) |
| Perceived stress | PSS-10 |
| Negative mental health | DASS-21 |
| Positive mental health | ORS-4 |
| Coping Behaviors | CISS-SFC |

A description of study instruments along with their reliability and validity are provided below:

The Perceived Stress Scale-10 Items (PSS-10) is a ten item self-reported scale to assess respondents’ global level of perceived stress (36). Respondents were required to rate the frequency of certain feelings they experienced over the past month on a 5-point Likert Scale (1=never, 2=rarely, 3=sometimes, 4=often, 5=always). It has shown to predict the range of health-related outcomes presumed to be associated with appraised stress (36). PSS-10 is a shorter version of Perceived Stress Scale 14-item (PSS-14) that assesses how respondents perceives their lives to be unpredictable, uncontrollable and overloaded (48). The PSS-10 has been validated in populations in different countries and proven to possesses adequate internal consistency with Cronbach’s alpha coefficients ranging from 0.67 to 0.91 (49-54), moderate convergent validity with stressful life events (55), and good concurrent validity with mental health problems such as anxiety and depression (56-58). Particularly, the PSS-10 has been translated in Chinese and shown acceptable reliability and validity in both adults (37, 38) and adolescents (39).

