### Statistical methods

Statistical analyses will be performed using SPSS 22.0 (SPSS Inc., Chicago, IL). We will present descriptive data in a table: categorical variables (e.g., gender, grade, home location etc.) will be presented as counts and percentages. Continuous variables (e.g., age, PSS-10, DASS-21, ORS-4 etc.) will be presented as mean and standard deviation (SD).

To determine whether any significant differences exist between intervention group and control group at baseline, independent t test will be conducted on continuous baseline variables (e.g., age, PSS-10, DASS-21, ORS-4, CISS-SFC, MER), and chi-square analyses will be conducted on categorical or nominal variables (e.g., gender, home location, guardian etc.).

To determine whether the intervention is effective, intention-to-treat (ITT) analyses will be conducted separately (59). The ITT analysis will include the data from the whole randomized sample. A linear mixed model (LMM) will be used to investigate the effects of time and groups on the primary outcome variables. The LMM will be performed with group, time, and group × time as fixed effects. Subjects and schools will be selected as random effects in order to take into consideration both within-subject and within-school correlations. Cohen d effect sizes will be calculated to examine the magnitude of between-group differences. Similar analyses will be conducted for exploring effects on secondary outcome measures.

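### The primary mixed model does not adjust for baseline PSS-10, so the 12-week effect is a difference in change scores: unbiased, but less precise than the data already collected would allow

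*Protocol*

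**What the plan says.** The Statistical methods section gives the full set of fixed effects for the primary outcome: "The LMM will be performed with group, time, and group × time as fixed effects". On random effects it says "Subjects and schools will be selected as random effects". The same form is carried over to the secondary outcomes.

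Under Data collection methods, the outcome measures "will be collected at baseline (T0=0 weeks), post-intervention (T1=12 weeks) and follow-up (T2=16 weeks"; Table 1 shows the same three visits for PSS-10. The Outcomes section defines success as "statistically significant more reduction in mean score of PSS-10 in the intervention group as compared with the control group at 12 weeks".

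Apart from the descriptive table and its place in the model as a visit, baseline PSS-10 is used only for a comparison of the arms at entry: "independent t test will be conducted on continuous baseline variables (e.g., age, PSS-10, DASS-21, ORS-4, CISS-SFC, MER".

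The Sample size section starts from a meta-analysis whose "overall mean effect size for stress at posttest was Cohen d=0.43" (95% CI 0.31–0.54). It finds that "a sample size of 172 (n=86 in each study group) is required to detect effect size of d=0.43 with a power (1− β) of 0.80", raises this to 96 per arm for 10% dropout, and then plans 150 per arm.

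**The concern.** The protocol does not list the levels of time. Three scheduled visits, and success defined as a reduction, make it natural to read T0 as one of them. On that reading the group term is an unrestricted difference between the arms at T0, and the effect at 12 weeks is the change from T0 to T1 in the app arm minus the same change in controls. If T0 were not a level of time, the model would not use the baseline score at all and would still be unadjusted.

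A difference in changes subtracts the whole T0 score, although only part of a T0 difference is expected to persist to T1. A baseline-adjusted analysis subtracts only the part that persists, and so has the smaller variance. The subject random intercept does not recover the loss, because the free group term absorbs the between-arm information at T0.

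At stake are the width of the confidence interval, power if the true effect is smaller than planned, and how far one realised estimate moves with a chance baseline difference between arms.

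**Working it through.** **Inputs.** From the protocol: d=0.43 (lower limit 0.31), power 0.80, alpha 0.05 (taken as two-sided), 86 per arm required, 150 per arm planned, SD 5.6. Assumed, because the protocol does not give it: the T0–T1 correlation r, over 0.3 to 0.7. Equal variances at T0 and T1 are also assumed.

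**The plan's own figure.** A two-sample t calculation with d=0.43, two-sided alpha 0.05 and power 0.80 gives 85.87, so 86 per arm and 172 in total. Allowing for dropout, 86/0.9 = 95.6, so 96 per arm. Both figures reproduce. This is a post-test comparison with the full SD, not a comparison of changes.

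**Variance of the 12-week contrast**, in units of the post-test variance:

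- As written (free T0 difference): 2(1−r)
- Baseline-adjusted: 1−r²
- Ratio, adjusted over as written: (1−r²)/[2(1−r)] = (1+r)/2

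| r | as written | adjusted | ratio | SE smaller by |
|---|---|---|---|---|
| 0.3 | 1.40 | 0.91 | 0.65 | 19% |
| 0.5 | 1.00 | 0.75 | 0.75 | 13% |
| 0.7 | 0.60 | 0.51 | 0.85 | 8% |

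A generalised least squares calculation with three visits and a subject random intercept, comparing a free with a common T0 mean, gives the same values. Equality with the raw difference in changes is exact for complete data and approximate when visits are missing.

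**Power**, two-sample t with effect d/√(variance), independent students, as written against adjusted:

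| n per arm, d | r=0.3 | r=0.5 |
|---|---|---|
| 150, d=0.43 | 88% vs 97% | 96% vs 99% |
| 150, d=0.31 | 62% vs 80% | 76% vs 87% |
| 86, d=0.43 | 66% vs 84% | 80% vs 90% |

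At 86 per arm the contrast as written reaches 80% only if r is about 0.5 or more, because 2(1−r) is at most 1 only when r is at least 0.5.

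**Chance imbalance.** If the app arm starts Δ points above control by chance, the expected shift in the change contrast, given that imbalance, is rΔ − Δ = −(1−r)Δ. With r=0.5 and Δ=1 point, that is half a point in favour of the app. Over all randomisations the shift averages zero.

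**Clustering.** Students are randomised by class. With an assumed 15 students per class, ICC 0.02 to 0.10, class autocorrelation 0.8 to 1 and r of 0.5 to 0.7, the variance as written is 1.07 to 1.28 times the adjusted variance. Without clustering it is 1.18 to 1.33 times (2/(1+r) at r=0.7 and 0.5). The gain shrinks but remains.

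**The case against.** The strongest reply is that the model is valid and answers the stated question. Success is defined as a greater reduction, and the group × time contrast of T1 against T0 estimates exactly that, without bias under randomisation. This stands: the point is one of efficiency, not validity.

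Second, the planned sample leaves a margin. With 150 per arm, or 135 after the protocol's 10% dropout, power at d=0.43 as written is about 88% or 85% at r=0.3, and 96% or 94% at r=0.5. A reader might infer from the 86-per-arm row that this trial is underpowered unless r reaches 0.5. The protocol does not support that, because 86 is its minimum and not its plan. At 150 per arm, 80% needs r of only about 0.13. The margin is not secure, however: the sample size makes no allowance for class clustering, and at d=0.31 the loss is material.

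Third, a reader might suppose that the model carries a chance baseline imbalance in full into the effect. It carries the fraction 1−r.

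Fourth, since "Students who are self-identified as feeling stressed will be recruited", a reader might expect regression to the mean to distort the result. Regression caused by that recruitment affects both randomised arms alike and cancels on average. What remains is the part tied to chance imbalance, already counted above.

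Fifth, a common T0 mean is safe only if T0 is measured before allocation is known, and the protocol leaves this unclear. Table 1 puts baseline and randomisation in one T0 column, data are collected through the app, Appendix 1 places PSS-10 in Session 1, and nobody is blinded after assignment. This objection stands and limits the remedy. The covariate form has its own cost: students with no follow-up score drop out of the likelihood, although the intention-to-treat analysis promises the whole randomised sample.

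**Conclusion.** The point holds as a loss of precision that can be avoided. It belongs to the protocol, because the protocol itself fixes the fixed effects. The adjusted variance is (1+r)/2 of the variance as written, or 65% to 85% for r of 0.3 to 0.7 with independent students, and the saving is smaller with class clustering. At the planned size and d=0.43 the power cost is modest, 3 to 9 percentage points for r of 0.5 to 0.3. At d=0.31 it is 11 to 18 points.

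This rests on T0 being a level of time (inferred), on equal variances at T0 and T1, on an r that the protocol does not give, and, for the power figures, on ignoring clustering. It does not show that the planned analysis is biased.

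**What to change.** In Statistical methods, state that the primary analysis adjusts for T0 PSS-10, in one of two forms:

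- Model T1 and T2 as outcomes, with group, time, group × time, T0 PSS-10 and T0 PSS-10 × time as fixed effects.
- Keep T0 as an outcome and constrain the arms to a common T0 mean: no group main effect, with group terms at T1 and T2 only. This also keeps students who have only T0 data. Use it only if T0 PSS-10 is completed before allocation is known, and say so in Table 1 and Data collection methods.

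Name the 12-week group contrast as primary. Use the same form for DASS-21, ORS and CISS-SFC, each with its own T0 score. The cost is one sentence in Statistical methods, plus a clarification of the order of T0 and allocation if the second form is chosen. No new data, visits or students are needed.

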## Trial design

A superiority, two-arm, cluster randomized controlled trial will be conducted (see Figure 1 for the flow chart of the trial design). Confirmed participants will be randomly allocated in a 1:1 ratio into one of the study groups. In the intervention group, the participants will use an online stress-managing program which will be delivered via smartphone. Participants in the control group will not use the online program duration. However, they will be notified that they will have access to the online program after 12 weeks (i.e., at the end of the study). The condition to which each participant will be allocated will not be blinded for either experimenters or participants.

[figure not shown]

Figure 1 Flow chat of the trial design

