# Methods

## Participants, interventions, and outcomes

### Study setting

This study will be conducted in two high schools: Mianyang Dongchen International School (MDIS) and Mianyang Nanshan High School (MNHS) in Mianyang City, Sichuan Province in China. MDIS is a private school and MHS is a public school.

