## Assignment of interventions

### Allocation

A two-arm randomized controlled trial will be conducted. Confirmed participants will be randomly allocated in a 1:1 ratio into one of the study groups. Students will be randomised within schools. In order to minimise contamination, students will be randomised on a class basis. Also, students will be notified that all of the participantas will have access to the online program, therefore they should not talk to each other about the content of the intervention. In the intervention group, the participants will use an online stress-managing program which will be delivered via smartphone. Participants in the control group will not use the online program duration. However, they will be notified that they will have access to the online program after 16 weeks (i.e., at the end of the study). The condition to which each participant will be allocated will not be blinded for either experimenters or participants.

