### Implementation

Clusters of students will be randomly assigned (1:1) to either the intervention of control condiction by use of computer-generated randomisation list prepared by a research assistant independent from the research groups. The participants will be enrolled by principal investigator (XZ), with the assistance of head teachers.

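### The primary mixed model has no term for class, the unit of randomisation, so its standard errors are too small whenever classes differ in how PSS-10 changes over time

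*Protocol*

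**What the plan says.** The Trial design section states: "A superiority, two-arm, cluster randomized controlled trial will be conducted". The Allocation section gives the level of randomisation in two sentences: "Students will be randomised within schools" and "In order to minimise contamination, students will be randomised on a class basis". The Implementation section confirms that clusters, not individuals, are assigned 1:1 from a computer-generated list. Study setting fixes the number of schools: "This study will be conducted in two high schools".

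Statistical methods then specifies the primary model. Its fixed part is: "The LMM will be performed with group, time, and group × time as fixed effects". Its random part is: "Subjects and schools will be selected as random effects in order to take into consideration both within-subject and within-school correlations". Secondary outcomes are to be analysed in a similar way. The protocol contains no class-level random effect, cluster-robust variance or analysis of class summaries.

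The Outcomes section defines success as a significantly greater reduction in mean PSS-10 in the intervention arm than in control at 12 weeks.

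**The concern.** In a cluster-randomised trial the analysis has to carry the variation between the units that were randomised. Here those units are classes. Students in a class share teachers, a timetable and exam dates, and may take up the app together, so their outcomes may move together. If they do, the students in a class are not independent replicates of the arm, and a model that treats them so understates the uncertainty of the group difference.

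Success is defined by statistical significance on PSS-10, so an understated standard error bears directly on the main claim. The same model structure carries over to the secondary outcomes.

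This is not a detail left for a statistical analysis plan. The protocol lists its random effects, says they are there to handle correlation, and chooses a level that does not match its own randomisation.

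**Working it through.** **1. The plan's own sample size.** Inputs from the Sample size section: d = 0.43, power 0.80, alpha 0.05, 86 per arm. A two-sided two-sample t-test gives 85.87, so 86 per arm and 172 in total. Allowing for 10% dropout, 86/0.9 gives 96 per arm and 192 in total. The number the protocol says "is required to detect effect size of d=0.43 with a power (1− β) of 0.80 with alpha of 0.05" is thus reproduced exactly as an individually randomised calculation, with a design effect of 1. Class is absent from the planning as well as from the model.

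**2. Why school does not help.** Randomisation is within school, so each school has both arms. A school intercept is added equally to both arms and cancels from their difference. Its variance would also be estimated from two levels, that is, on 1 degree of freedom. A class, by contrast, lies wholly in one arm, so class variation stays in the estimated difference.

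**3. Which class variation matters.** Write the class contribution as a constant part plus a part that varies by time point. With baseline (T0) as an outcome, the constant part subtracts out of the T0-to-T1 contrast and the time-varying part does not. If the class × time share of total variance is c and the baseline to 12-week correlation is r, the ICC of the change is c/(1 − r).

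**4. Formula.** Let m be trial participants per class (equal sizes) and ICC the within-class correlation of the tested contrast. Then:
- design effect DE = 1 + (m − 1) × ICC
- standard error understated by a factor √DE
- actual two-sided type I error = 2[1 − Φ(1.96/√DE)]

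The protocol gives neither m nor ICC. Both are assumed.

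| m | ICC | DE | √DE | Actual type I error |
|---|---|---|---|---|
| 2 | 0.02 | 1.02 | 1.01 | 5.2% |
| 2 | 0.05 | 1.05 | 1.02 | 5.6% |
| 3 | 0.02 | 1.04 | 1.02 | 5.5% |
| 3 | 0.05 | 1.10 | 1.05 | 6.2% |
| 5 | 0.05 | 1.20 | 1.10 | 7.4% |
| 10 | 0.05 | 1.45 | 1.20 | 10.4% |
| 15 | 0.05 | 1.70 | 1.30 | 13.3% |
| 25 | 0.02 | 1.48 | 1.22 | 10.7% |
| 25 | 0.05 | 2.20 | 1.48 | 18.6% |
| 25 | 0.10 | 3.40 | 1.84 | 28.8% |

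**5. Simulation of the T0-to-T1 contrast.** The setting was 300 students in two schools, with classes randomised within school, school adjusted for and class ignored.
- Class share 0.05, all constant over time: about 5% at m=25, so no inflation.
- Class × time share 0.01 (constant share 0.04): about 11-12% at m=25.
- Class × time share 0.02 (constant share 0.03): about 7% at m=5 and 16-18% at m=25.

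The ranges at m=25 correspond to r between 0.5 and 0.6, also assumed. The formula agrees: with c = 0.02 and r = 0.5 the ICC of the change is 0.04, DE = 1 + 24 × 0.04 = 1.96, and the error is 2[1 − Φ(1.96/1.40)] = 16%.

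If the comparison were made on the 12-week score alone, constant class effects would not cancel: a constant share of 0.05 gave about 19% at m=25.

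**The case against.** The best defence is that the planned model already removes much of the class effect. Baseline is one of the outcomes, so stable differences between classes leave the T0-to-T1 contrast, and some of what classmates share is stable. This is correct. A reader might infer that the standard errors are too small in every case and that the false-positive rate must exceed 5%. The documents do not support that: with purely constant class effects the type I error stays at about 5%. What survives is the part that varies over time, and nothing in the protocol rules it out.

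The second defence is that few students may come from each class. Recruitment is voluntary, by posters, flyers and announcements, among more than 2000 plus more than 3500 students, and 300 is at most about 5.5% of that pool (300/5500). If recruits are spread thinly, m could be 2 or 3 and the inflation slight. This also stands as a limit on size. But the protocol neither caps nor predicts the number per class, and m=25 would mean only 12 classes in the whole trial (300/25).

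A third possible defence is that the text also speaks of allocating confirmed participants 1:1, which could be read as individual randomisation. Trial design, Allocation and Implementation taken together do not allow that reading.

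Two further criticisms are tempting but do not belong to the defect. One is that a 2-degree-of-freedom group × time test could succeed on week 16 alone. Statistical methods does not say that such a test decides success, and Outcomes already places the comparison at 12 weeks. The other is that a change-score contrast is invalid. Under randomisation it is unbiased; adjusting for baseline improves precision and does not correct validity.

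**Conclusion.** The omission is certain and should be corrected before analysis: classes are randomised, the model names its random effects, and class is not among them. The direction is also clear, since any positive within-class correlation in the tested contrast makes the reported standard error too small. For the planned change from baseline, this requires classes to differ in their change over time.

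The size cannot be fixed from the protocol. It runs from negligible (5-6% at m of 2-3, ICC 0.02-0.05) to serious (19-29% at m=25, ICC 0.05-0.10). Those figures assume equal class sizes and a normal approximation. The high end is a scenario, not an estimate for this trial.

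**What to change.** - Record each participant's class at enrolment. Without it the error cannot be repaired later.
- Add random effects for class (nested in school) and class × time. A class intercept alone is not enough while baseline is an outcome, because it cancels in the T0-to-T1 contrast.
- Enter school as a fixed two-level stratum instead of a random effect.
- Use Satterthwaite or Kenward-Roger degrees of freedom, since the number of classes may be small.
- Name the group contrast at 12 weeks, already the success criterion in Outcomes, as the single primary test.
- Use the same structure for the secondary outcomes.

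**Cost.** Protocol wording and one extra data field. Intervals widen and power is lower than under an analysis that ignores class. At 150 per arm and d = 0.43, before dropout, power is 96% with no clustering, 82% at m=15 and ICC 0.05, 71% at m=25 and ICC 0.05, and 52% at m=25 and ICC 0.10 (m and ICC assumed; the degrees-of-freedom correction would lower these a little further).

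**Optional, for precision only.** Use baseline PSS-10 as a covariate instead of an outcome. At the individual level, with equal variances, the variance of the change score relative to the adjusted contrast is 2(1 − r)/(1 − r²) = 2/(1 + r). That is 1.33 at r = 0.5, and 1.43 to 1.18 for r from 0.4 to 0.7 (r assumed). Class must still be in the model, because constant class effects then no longer cancel fully.

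### The subject random effect, read in the ordinary way, gives all pairs of unequally spaced visits one common correlation, so the standard error of the 12-week change may be misstated; an unstructured covariance removes the risk at almost no cost

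*Protocol*

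**What the plan says.** The Protocol plans a linear mixed model (Statistical methods): "The LMM will be performed with group, time, and group × time as fixed effects". The dependence between a student's repeated measurements is assigned to a random effect: "Subjects and schools will be selected as random effects in order to take into consideration both within-subject and within-school correlations". The section does not say whether the subject effect is an intercept only, whether time is categorical or linear, or whether the residuals have a covariance structure of their own. The same approach is carried over to the secondary outcomes.

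Measurements are taken at "baseline (T0=0 weeks), post-intervention (T1=12 weeks) and follow-up (T2=16 weeks" (Data collection methods), so the gaps are 12 weeks (T0 to T1), 4 weeks (T1 to T2) and 16 weeks (T0 to T2).

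Success on the primary outcome is defined as "statistically significant more reduction in mean score of PSS-10 in the intervention group as compared with the control group at 12 weeks" (Outcomes).

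The only information on spread is a single SD in the Sample size section: "a population mean PSS-10 of 13.7 (SD=5.6) equal between groups (47". No correlation between visits and no SD by visit is given.

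**The concern.** A random intercept with independent residuals implies compound symmetry: equal variances at T0, T1 and T2, and one correlation shared by T0-T1, T0-T2 and T1-T2. There are three reasons to expect the closest pair, T1-T2, to be more alike than the other two.

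- It is 4 weeks apart, against 12 and 16 weeks.
- The PSS-10 asks about the past month, so the T1 and T2 answers cover adjacent months.
- A lasting shift in a student's stress after T0, for example from varying response or a change in the school term, adds to the variance of T0-T1 and T0-T2 but not to that of T1-T2.

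The model pools the three pairs. If T1-T2 is the most stable, it lends the 12-week change precision that the change does not have. Because success is a significance statement about that change, an SE error feeds straight into the false-positive rate. The T1-T2 comparison is affected in the opposite direction. All this concerns repeated measures within a student and would arise even without clustering by class.

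**Working it through.** **Inputs from the Protocol.** SD 5.6; 150 students per arm ("we will choose a sample size of 300 (n=150 for each study group"); visits at 0, 12 and 16 weeks; contrast of interest T1 minus T0 between arms. **Assumed, because the Protocol gives none:** the correlations r01, r02 and r12 between T0-T1, T0-T2 and T1-T2, and any difference in SD between visits. Complete data and categorical time are assumed, and class clustering is set aside.

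**The plan's own figure first.** The Protocol says that 172 students, 86 per arm, "is required to detect effect size of d=0.43 with a power (1− β) of 0.80 with alpha of 0.05". A two-sided two-sample t-test with d = 0.43 gives 85.87, hence 86 per arm and 172 in total. With 10% dropout, 172/0.9 = 191.1, rounded up to 192 for equal arms, which agrees with "A sample size of 192 (n=96 in each study group) will be needed when allowing for 10% drop out". Both figures reproduce. They come from a comparison of two independent means, so they tell us nothing about the within-student correlation.

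**Formula.** Let Vij = SDi² + SDj² − 2·rij·SDi·SDj be the variance of the change between visits i and j. The correct variance of the 12-week change is V01. Under a random intercept with independent residuals, the model uses (V01 + V02 + V12)/3. Hence

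- SE ratio (model/true) = √[(V01 + V02 + V12)/(3·V01)];
- with equal SDs this is √[(1 − mean r)/(1 − r01)];
- real two-sided type I error = 2·[1 − Φ(1.96 × ratio)].

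The SE is too small only if V02 + V12 < 2·V01. With equal SDs that means r02 + r12 > 2·r01.

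**Worked example.** Take exponential decay with a 4-week correlation of 0.8: r01 = 0.8³ = 0.512, r02 = 0.8⁴ = 0.410, r12 = 0.800, mean 0.574.

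- V01 = 2 × 31.36 × 0.488 = 30.61, so the true SE is √(2 × 30.61/150) = 0.639.
- The model variance is 2 × 31.36 × 0.426 = 26.73, so the model SE is √(2 × 26.73/150) = 0.597.
- The ratio is 0.934 and the type I error 6.7%. In 20,000 simulated trials the rejection rate was 6.65%, against 5.0% with the variance of the change estimated directly.

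**Range of assumptions.**

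| Pattern (r01 / r02 / r12) | SE ratio | Type I error |
|---|---|---|
| Exponential decay, 4-week correlation 0.5 to 0.95 | 0.933 to 0.940 | 6.5 to 6.7% |
| 0.40 / 0.40 / 0.70 | 0.913 | 7.4% |
| 0.50 / 0.45 / 0.70 | 0.949 | 6.3% |
| 0.60 / 0.55 / 0.75 | 0.957 | 6.1% |
| 0.60 / 0.55 / 0.70 | 0.979 | 5.5% |
| 0.50 / 0.45 / 0.60 | 0.983 | 5.4% |
| 0.50 / 0.50 / 0.50 | 1.000 | 5.0% |
| 0.60 / 0.50 / 0.65 | 1.021 | 4.6% |
| 0.50 / 0.45 / 0.60, SD 6.2 at T2 | 1.021 | 4.5% |
| 0.55 / 0.40 / 0.60, SDs 5.0 / 5.6 / 6.5 | 1.123 | 2.8% |

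The last row in numbers: V01 = 25.56, V02 = 41.25, V12 = 29.93, mean 32.25, and √(32.25/25.56) = 1.123.

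Simulation with 135 per arm (10% dropout from 150) gave 7.5%, 6.5%, 6.2% and 5.3% for 0.40/0.40/0.70, 0.50/0.45/0.70, 0.60/0.55/0.75 and 0.50/0.45/0.60, close to the formula.

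**Lasting shift without serial decay.** Take SD 5.6, a common correlation of 0.6, and a persistent individual shift after T0 with SD 2.8. Then V01 = V02 = 2 × 31.36 × 0.4 + 7.84 = 32.9 and V12 = 25.1, with mean 30.3. The ratio is 0.96 and the type I error about 6%.

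**The T1-T2 change.** The same formula with V12 in the denominator gives SE ratios of 1.10 to 1.29 in those four simulated patterns, so that SE is too large.

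**The case against.** The strongest reply is that the Protocol never writes intercept, independent residuals or equal variances. The SPSS mixed procedure can carry a residual covariance, and such detail is commonly left to the statistical analysis plan. This stands in part: the restriction is implied, not stated. But the section is not silent. It assigns the within-subject correlation to the subject effect and names nothing else, so an analyst who follows it as written fits one common correlation.

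A reader might go further and infer that the unequal spacing forces the SE to be too small, making the 12-week p-value too small and its interval too narrow. The documents do not support that. They give no correlations and no SDs by visit, and the table shows that concave decay or a larger SD at T2 reverses the sign. Downward error is the likelier direction when SDs are equal, because linear or convex decay of the correlation then satisfies the condition, but it is not certain.

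The Protocol also leaves open what happens between T1 and T2. Trial design and Interventions give controls access to the app after 12 weeks, Allocation after 16 weeks. These passages need to be reconciled. If controls can use the app in that interval, a high T1-T2 correlation and an unchanged T2 SD cannot be taken for granted in that arm.

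Finally, the effect is modest. A separate and probably larger issue is that classes are randomised but class is not in the model.

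**Conclusion.** The point holds in a limited form. Followed as written, the model imposes equal variances and one correlation on visits at 0, 12 and 16 weeks, and the SE of the contrast that defines success may be misstated. Under equal SDs and decaying correlation it is probably about 2 to 9% too small (type I error about 5.4 to 7.4% by formula, 5.3 to 7.5% by simulation). It is correct under equal correlations. In the reversed patterns it is about 2 to 12% too large (type I error about 4.6 down to 2.8%). Every one of these figures rests on assumed correlations and SDs.

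This does not make the primary analysis invalid. It is a restriction that the trial does not need, placed on its deciding contrast, and removing it guards against error in either direction.

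**What to change.** In Statistical methods, state that time is categorical with three levels. Replace the subject random intercept by an unstructured residual covariance of the three visits within student (REPEATED statement in SPSS MIXED, subject = student). State that the 12-week comparison is the T1-minus-T0 component of the group × time term. Apply the same wording to the secondary outcomes.

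The cost is one line of text and six covariance parameters instead of two for the within-student part, which is negligible with 300 students.

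Do not add a school effect that varies by visit: there are only two schools, so its variance could hardly be estimated. The missing effect for the randomised class should be dealt with as its own point; this change does not resolve it.
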